### Statistical Considerations

#### Analysis Population

An intention-to-treat (ITT) analysis population will comprise all patients who have been randomized and who have reached the intervention period (the 24 h immediately after the end of LTx surgery), the so-called modified ITT. Patients who were randomized but did not undergo LTx surgery, who died during surgery, or who did not reach the intervention period for any reason will not be included in this population. Analyses based on this population (modified ITT) will group patients according to the treatment they were randomized to receive, regardless of the actual treatment received. We do not expect missing data for the primary outcome variables. Any missing data will be handled as recommended by Jakobsen et al [27]*.*

#### Descriptive Statistics

Normally distributed continuous data will be presented as the mean (SD) and 95% CIs. Nonnormally distributed continuous data will be presented as the median, IQR, and 95% CIs. Categorical and binary data will be presented as a percentage with CIs, and as absolute numbers. Ordered categorical variables will be presented as the median, IQR, and 95% CIs.

#### Statistical Design, Method, and Analytical Procedures

All statistical analyses will be performed by an independent statistician. Treatment allocation will remain concealed during the initial analysis, with the 2 groups labelled as “group A” and “group B,” ensuring a blinded statistical analysis. All statistical tests will be 2-sided. The distribution of continuous variables will be determined by visual inspection of histograms and quantile-quantile plots. The primary outcome will be based on the mean highest PaO_2_/FiO_2_ ratio within the first 72 hours (a continuous variable). Differences between treatment groups in the mean highest PaO_2_/FiO_2_ ratio within the first 72 hours will be compared using a multivariate linear regression model adjusted for, at minimum, the stratification variables (site, age, and gender). Continuous variables, ordered categorical variables, and binary variables measured over time will be compared using mixed models for repeated measures. The distribution of the data will be checked using quantile-quantile plots, and if the data are skewed, then a generalized linear mixed effects model with the appropriate distribution will be used. A random intercept will be applied at the patient level. We will check model assumptions for each model. Kaplan-Meier survival analysis will be performed for mortality data up to 48 months after transplantation. Median QOL scores from each instrument (ordinal variables) will be compared using the Mann-Whitney *U* test at each time point. Subgroups for analysis shall be described in detail in the statistical analysis plan.

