### Outcomes

#### Primary Performance End Point

The primary end point is the oxygenation ratio, defined as the highest PaO_2_/FiO_2_ ratio within 72 hours after LTx.

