### Methodology

#### Medical Chart Review

The following data will be collected from medical charts at specified timepoints: background variables (demographics, comorbidities, therapies, and perioperative data), FiO_2_ measurements (baseline and 0-72 h after transplantation, adjusted for ventilation), arterial blood gas measurements (baseline and d 1-3 after transplantation), radiological assessments (infiltrates and edema at d 1-3), PGD severity (d 1-3 using a 0-3 scale), total norepinephrine dosage (first 72 h), lung carbon monoxide diffusion capacity (baseline, 6, 12, 24, and 48 mo), spirometry (forced expiratory volume, forced vital capacity, total lung capacity at 1, 3, 6, 12, 24, and 48 mo), chest CT findings (1, 3, 6, 12, 24, 36, and 48 mo), CLAD assessment (presence and subtype up to 48 mo), renal function (serum creatinine, glomerular filtration rate, need for renal replacement therapy at specified intervals), urea levels (d 1-3), iohexol clearance (3, 6, 9, 12, 24, 36, and 48 mo), mortality data (up to 48 mo), acute rejection episodes (occurrence and type up to 48 mo), immunosuppressant levels (first 72 h), adverse events, and SAEs.

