#### Level of Significance and Power

In the interim analysis (described below), the DSMB will use Pocock stopping boundaries (*P*<.03). Therefore, the 2-sided α value in the final analysis will be *P*=.03. We will use a power of 0.8 (80%).

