#### Sample Size

The power calculation, performed using GPower 3.1 (AdvanSci Research Solutions), is based on superiority analysis assumptions for the primary end point (improved oxygenation ratio, defined as the highest PaO_2_/FiO_2_ ratio measured within 72 h after LTx). Based on data from a cohort of patients undergoing LTx from Skåne University Hospital in Lund from 2011 to 2020, we estimate that the mean PaO_2_/FiO_2_ value in the control group will be approximately 300 (SD 100) mm Hg and that values will be normally distributed. We estimate that the average PaO_2_/FiO_2_ value will be 60 (SD 100) mm Hg higher (effect size) in the treatment group compared with the control group.

The sample size was calculated using a 2-tailed *t* test to compare the PaO_2_/FiO_2_ values in the treatment versus control groups. We will require 52 participants in each group to achieve the power and α level detailed above. We will add 10% of the required sample size to account for possible dropouts, withdrawal of consent, or mortality in the first 72 hours. Thus, we aim to recruit 58 patients in each group to a total of 116 participants. With this number of participants, we estimate that all secondary outcome variables will have a power of at least 80% at an α level of .05.

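### The 72-hour maximum can be an untreated end-of-surgery value, and the primary model does not name that starting oxygenation as a covariate

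*Protocol article*

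**What the plan says.** All references are to the protocol article.

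- **End point** (Primary Performance End Point): the oxygenation ratio, "defined as the highest PaO_2_/FiO_2_ ratio within 72 hours after LTx". No lower limit is set on when in the window the value may be taken.
- **Device timing** (Intervention): 12 hours of filtration, continuous or interrupted, inside the 24 hours that follow the end of surgery. No start time relative to any blood gas is given.
- **Data** (Medical Chart Review): FiO2 is collected at "baseline and 0-72 h after transplantation, adjusted for ventilation". Arterial gases are listed at baseline and on days 1 to 3. No separate first postoperative, pre-device gas is named.
- **Model** (Statistical Design, Method, and Analytical Procedures): a "multivariate linear regression model adjusted for, at minimum, the stratification variables (site, age, and gender"). The Limitations section adds multivariate adjustment for demographic characteristics and concomitant medication. Neither place names early graft oxygenation.
- **Sample size** (Sample Size; Level of Significance and Power): control mean "approximately 300 (SD 100) mm Hg"; the treated mean "will be 60 (SD 100) mm Hg higher (effect size) in the treatment group"; "the 2-sided α value in the final analysis will be *P*=.03"; 80% power; 52 per group, recruited as 58 per group.

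**The concern.** A maximum takes whichever value in the window is largest. The filter cannot have influenced a gas drawn at the end of surgery, yet that gas is eligible to be the outcome. It is more likely to be the maximum when later values are lower. If filtration raises later values, this happens more often in the control arm, so the untreated value lifts the control mean more than the treated mean. The difference between arms shrinks.

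The same value could do useful work elsewhere. It describes the graft before treatment, and adjusting for it would remove between-patient variance from the primary comparison. Site, age and gender do not measure graft function directly.

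**Working it through.** **1. The plan's own figure.** Two-sided t test, difference 60, SD 100 (standardised difference 0.6), α = 0.03. Noncentrality = 0.6 × √(n/2). With n = 52 per arm this is 0.6 × √26 = 3.06, and power from the noncentral t with 102 degrees of freedom is 0.803. With n = 51 it is 0.795. So 52 per arm reproduces. Adding 10% gives 57.2, rounded up to 58 per arm and 116 in total.

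**2. Is the end-of-surgery value both untreated and inside the window?** Connection is described only after the end of surgery, so a gas at that moment precedes filtration in both arms. The window is the 72 hours after LTx and FiO2 is collected from hour 0, so the value is eligible for the maximum. With 12 hours of filtration to fit into 24, up to about 12 hours of unfiltered values could be eligible (24 − 12 = 12).

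**3. Dilution (illustrative).** Assumptions, none of them in the document: the untreated value X and the later maximum Y are normal with SD 100 and correlation 0.5; Y is 60 higher under filtration and X is unchanged; X averages g below the control mean of Y. The SD of Y − X is then θ = 100 × √(2 − 2 × 0.5) = 100. Including X raises the expected outcome by θ[φ(z) − zΦ(−z)], where z = gap/θ. The share of patients whose outcome is X is Φ(−z).

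| g | Share with X as outcome (control / treated) | Lift (control / treated) | Difference | Power at 52 |
|---|---|---|---|---|
| 100 | 16% / 5% | 8.3 / 2.3 | 60 + 2.3 − 8.3 = 54.0 | 0.74 |
| 50 | 31% / 14% | 19.8 / 6.9 | 60 + 6.9 − 19.8 = 47.1 | 0.64 |

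Power uses the SD of the resulting maximum (about 97 and 94) and was confirmed by simulation. With g = 150 the difference is 57.7 and power 0.78, so the loss is small when later values are much higher than the first.

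**4. Precision from the covariate.** Residual SD = 100 × √(1 − ρ²), n = 52 per arm, α = 0.03, difference 60, 101 degrees of freedom. The correlation ρ between the end-of-surgery ratio and the outcome is an assumption.

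| ρ | Residual variance | Residual SD | Power |
|---|---|---|---|
| 0 | 100% | 100 | 0.80 |
| 0.3 | 91% | 95.4 | 0.84 |
| 0.4 | 84% | 91.7 | 0.87 |
| 0.5 | 75% | 86.6 | 0.91 |
| 0.6 | 64% | 80.0 | 0.95 |

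**5. Why the timing of the covariate matters.** Suppose the covariate is taken after connection and already carries a fraction f of the effect. The adjusted estimate is then 60 × (1 − ρf). With ρ = 0.5 and f = 0.5 it is 60 × 0.75 = 45 mm Hg, with power 0.66. With f = 1 it is 30 mm Hg, with power 0.31. Both are worse than no adjustment.

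**The case against.** The case against is substantial.

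- **The covariate list is open.** A reader might infer that the model adjusts for the stratification variables alone. The text gives them as a minimum, the Limitations section foresees more, and the SAP is not shown. This stands: the missing covariate is not an error in the protocol.
- **The value may not be ready to use.** A reader might infer that the trial already holds a first postoperative, pre-device ratio. The chart-review list does not name one. This stands in part: a 72-hour maximum needs paired PaO2 and FiO2 readings, so such a gas probably exists in the charts, but its timing has to be defined.
- **Adjustment is not free.** Randomisation precedes surgery and treating staff are unblinded, so any postoperative value is post-randomisation, and one taken after connection would absorb part of the effect (step 5). The attenuation does not apply to a value taken before connection, but that timing must be enforced.
- **The trial meets its stated power without this.** Correct. The sample size rests on an unadjusted t test and needs no covariate gain. The assumed 60 mm Hg is also stated for the 72-hour maximum itself. If it was derived with untreated values included, the dilution is already in it, and removing them would help rather than repair a shortfall.
- **Changing the window changes the end point.** Correct; that needs a protocol amendment, not only a line in the SAP.

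None of this answers the window problem. It is fixed in the end-point definition, which an SAP would not normally alter.

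**Conclusion.** The point holds as one about end-point definition, with a conditional gain in precision attached. As worded, the end point can be filled by a value the device could not have affected. If filtration raises later values, the direction of the error, towards no difference, follows from taking a maximum. Its size does not: 60 becoming about 54 or 47 mm Hg rests on an assumed gap of 100 or 50 mm Hg, a correlation of 0.5, normality, and 60 mm Hg being the effect on post-connection values. The power gain to between 0.84 and 0.95 rests on an assumed correlation of 0.3 to 0.6 and on the covariate preceding filtration.

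The documents do not support saying that the sample size is wrong, that the covariate list is closed, or that the adjustment costs nothing.

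**What to change.** 1. Define one end-of-surgery PaO2/FiO2 by the same clock rule in both arms: the first arterial gas at or after the end of surgery and before any device connection.
2. Exclude that value from the 72-hour maximum in both arms.
3. Prespecify it, before the interim analysis, as a covariate alongside site, age and gender in the interim and final primary models.
4. State that no value taken after connection may serve as the covariate. Where the first gas follows connection, treat the covariate as missing under a rule fixed in advance.

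**Cost.** A small amendment to the end-point wording, plus SAP text. Gas time and connection time must be taken from the charts. The covariate precedes treatment but follows randomisation, which should be acknowledged. Other unfiltered values between that gas and connection stay in the window. Removing them by actual connection time would give the arms unequal windows, because controls have no connection time, so some dilution may remain. The sample size need not change.

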## Introduction

Lung transplantation (LTx) remains the standard option for treating patients with irreversible end-stage pulmonary disease [1]. Of all transplanted organs, the mean 5-year survival is the lowest following LTx [2]. The high mortality is highly associated with primary graft dysfunction (PGD), which arises in the first 72 hours after LTx and can lead to chronic lung allograft dysfunction (CLAD) within the first 3-5 years [3]. The cumulative incidence of these 2 conditions is between 40% and 80%. The fear of PGD leads to a low use rate of donated lungs, with only 20% of donated lungs being used [4].

PGD is reflected in the oxygenation capacity of the lung, measured as the ratio of the partial pressure of oxygen (PaO_2_) to the fraction of inspired oxygen (FiO_2_), which decreases with increasing PGD severity [2]. PGD is diagnosed according to International Society for Heart and Lung Transplantation guidelines [5] if the PaO_2_/FiO_2_ ratio drops below 300 and radiographic infiltrates are present in the lungs, consistent with pulmonary edema. Consequently, increasing the PaO_2_/FiO_2_ ratio following LTx is critical and may directly impact survival.

There is a general lack of effective treatments for both PGD and CLAD. When a transplanted lung is not accepted by the immune system in the recipient, a systemic inflammatory response starts where cytokines play a critical role in initiating, amplifying, and maintaining the inflammation leading to PGD [6]. Cytokine filtration can remove these cytokines from the circulation, thus reducing inflammation. Cytokine filtration devices have been shown in vitro and in vivo during orthotopic heart transplantation and kidney transplantation to target and reduce levels of medium– and low–molecular-weight molecules, such as cytokines, pathogen-associated molecular pattern molecules, and damage-associated molecular patterns [7-9]. Other than our feasibility study (ClinicalTrials.gov; NCT05242289) and a case series using extracorporeal cytokine adsorption therapy as rescue after LTx [10], this tool has not been applied to human LTx.

In this study, we want to test whether cytokine filtration improves outcome if administered in conjunction with LTx, for 12 hours in the first 24 hours following the procedure.

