#### Secondary Performance End Points

The secondary end points are (1) plasma levels of inflammatory markers: interleukin (IL)-10, IL-1β, soluble IL-2 receptor, IL-6, IL-8, and tumor necrosis factor α before and immediately after transplantation and at 6, 12, 24, 48, and 72 hours after transplantation and C-reactive protein and white blood cells before and immediately after transplantation and at day 1, 2, and 3 after transplantation; (2) infiltrates and oedema measured by chest x-ray or CT scan of the thorax at day 1, 2, and 3 after transplantation; (3) highest daily arterial blood gas measurements recorded on day 1, 2, and 3 after transplantation, as a measure of lung function; (4) PGD severity as evaluated per standard clinical procedures using a rating scale from 0 to 3 on day 1, 2, and 3 after transplantation, as a measure of lung function; (5) presence of any grade of PGD on day 1, 2, and 3 after transplantation, as a measure of lung function; (6) total dose of norepinephrine administered in the first 72 hours; (7) mortality up to 48 months after transplantation; (8) lung diffusion capacity, measured by carbon monoxide diffusion, at 6, 12, 24, and 48 months after transplantation, as a measure of lung function; (9) forced expiratory volume, forced vital capacity, and total lung capacity measured by spirometry at 1, 3, 6, 12, 24, and 48 months after transplantation, as a measure of lung function; (10) occurrence of any acute rejection episodes (clinically treated and/or biopsy verified) up to 48 months after transplantation, as a measure of lung function; (11) chest CT findings at 1, 3, 6, 12, 24, 36, and 48 months after transplantation; (12) the presence of any CLAD and CLAD subtypes up to 48 months after transplantation, as a measure of lung function; (13) kidney function evaluated by measurement of serum creatinine levels; calculated glomerular filtration rate and need for renal replacement therapy on day 1, 2, and 3 and at 1, 3, 6, 9, 12, 24, and 48 months after transplantation; urea levels on day 1, 2, and 3 after transplantation; and iohexol-clearance at 3, 6, 9, 12, 24, 36, and 48 months after transplantation; and (14) QOL evaluated by the 36-Item Short Form Health Survey at 24 and 48 months after transplantation.

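### Death is not accounted for in the 48-month comparisons of CLAD, acute rejection and quality of life, so these secondary comparisons would tend to favour whichever arm has more deaths

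*Protocol article*

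**What the plan says.** The Statistical Design, Method, and Analytical Procedures section sorts the outcomes by type:

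- **Mortality:** "Kaplan-Meier survival analysis will be performed for mortality data up to 48 months after transplantation". No other outcome is given a time-to-event method.
- **Outcomes over time:** "Continuous variables, ordered categorical variables, and binary variables measured over time will be compared using mixed models for repeated measures", with a random intercept per patient and a generalized version if the data are skewed.
- **QOL:** "Median QOL scores from each instrument (ordinal variables) will be compared using the Mann-Whitney *U* test at each time point".

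Under Secondary Performance End Points, item 10 is "occurrence of any acute rejection episodes (clinically treated and/or biopsy verified) up to 48 months after transplantation" and item 12 is "the presence of any CLAD and CLAD subtypes up to 48 months after transplantation". QOL (item 14) is measured at 24 and 48 months.

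Three other places come near the question without settling it. Analysis Population refers to published general guidance on missing data. Expected Dropout Rates foresees few long-term dropouts and does not mention long-term death. Sample Size allows for mortality only in the first 72 hours.

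On survival itself, the Introduction says "Of all transplanted organs, the mean 5-year survival is the lowest following LTx", and the Discussion (Overview) lists lower mortality among the expected benefits of the device.

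**The concern.** CLAD and first acute rejection are events that a patient can have only while alive. A patient who dies at month 8 without CLAD did not stay free of CLAD to month 48, and the later CLAD status is not a missing value, because it does not exist. A repeated-measures model for a binary variable has no natural place for this. Depending on data set-up, the early death is either counted as event-free or treated as unobserved. The same holds for QOL: a Mann-Whitney test on scores at 24 and 48 months can use only people who lived to give a score.

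If deaths were equal in the two arms, this would matter little for the comparison. The sponsor's own hypothesis is that they will not be equal. If filtration saves lives, its arm has more person-time in which CLAD and rejection can appear, and its QOL sample probably includes frailer survivors. If filtration costs lives, the same mechanism flatters it. CLAD, rejection and QOL are named secondary endpoints, and QOL is part of the stated purpose of showing superiority, so the reader of the results needs to know which effect is being shown.

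**Working it through.** **The plan's own figure.** The document gives no 48-month death, CLAD or QOL rate, so there is none to reproduce on this point. The stated sample size does reproduce: a difference of 60, SD 100, two-sided alpha 0.03 and power 0.80 give 52 per group by the exact t test (power 0.803; 51 per group gives 0.795). Adding 10% gives 58. That calculation concerns the 72-hour primary endpoint and is untouched here.

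**CLAD: assumed inputs.** Constant hazards over T = 4 years and the same CLAD hazard h in both arms. The net 48-month CLAD risk (risk if nobody died first) is 40% or 50%. Death without CLAD by 48 months, taken alone, is 20% in one arm and 30% or 40% in the other.

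Hazards: h = -ln(1 - net risk)/4, which is 0.1277 per year at 40% and 0.1733 at 50%. Death: d = -ln(1 - m)/4, which is 0.0558 at m = 20%, 0.0892 at 30% and 0.1277 at 40%.

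Observed CLAD by 48 months = h/(h + d) × (1 - exp(-4(h + d))).

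For net risk 40%:
- m = 20%: 0.696 × (1 - 0.480) = 36.2%
- m = 30%: 0.589 × (1 - 0.420) = 34.2%
- m = 40%: 0.500 × (1 - 0.360) = 32.0%

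For net risk 50%:
- m = 20%: 45.4%
- m = 30%: 42.9%
- m = 40%: 40.3%

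The arm with more deaths therefore shows 2.0 to 5.1 points less CLAD although the hazards are identical. A cause-specific hazard ratio would be 1 by construction.

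Against sampling error this is small. With 58 per arm, the standard error of 36.2% v 32.0% is √(0.362 × 0.638/58 + 0.320 × 0.680/58) = 8.8 points.

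The calculation counts people who died without CLAD as event-free. If CLAD is instead compared among those alive at 48 months, distortion arises only if CLAD and death are related. In simulation with baseline death risks of 15% v 30%, prevalence among survivors was 40% v 40% when they were unrelated, and 36% v 32% when CLAD tripled the death hazard.

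**QOL: assumed inputs.** 58 per arm, 3,000 simulated trials per setting, no treatment effect on QOL, two-sided P<.05. A latent survival score correlates 0.5 or 0.8 with QOL. The table shows the share of trials significantly favouring the arm with more deaths.

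| Deaths by arm | Correlation | Survivors only | Deaths ranked worst |
|---|---|---|---|
| 20% v 20% | 0.5 / 0.8 | 2.4% / 2.2% | 2.4% / 2.1% |
| 20% v 30% | 0.5 / 0.8 | 5.2% / 8.4% | 0.4% / 0.6% |
| 20% v 40% | 0.5 / 0.8 | 9.3% / 23.0% | 0.03% / 0.2% |

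The equal-mortality row is a reference: 2.5% is expected in one direction, and neither arm there has more deaths.

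**What worst-rank does and does not do.** With 52 per arm, deaths of 15% v 35%, correlation 0.5 and no QOL effect, the worst-rank test still rejects in about 26% of trials, because it picks up the mortality difference. With equal 25% mortality and a true QOL gain of 0.3 SD, it lowers power from about 28% (survivors only) to about 15%. It answers a composite question.

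**The case against.** Several points on the other side have weight.

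- **The mixed-model sentence does not name CLAD or rejection.** It speaks of variables measured over time and fits daily PGD presence better. This stands: the sentence reaches CLAD and rejection only by inference, because no other method is named for them. A reader might infer that the plan has decided to count early deaths as CLAD-free. The document does not say so.
- **A statistical analysis plan may settle it.** Handling of death for individual secondary endpoints is often left there. This lowers the weight of the point but does not remove it. The article fixes methods by outcome type and, in this section, leaves only subgroups to the analysis plan. The methods it fixes do not accommodate death, and general missing-data guidance does not fit a value that cannot exist.
- **All sizes are assumed, and the CLAD gap is within noise.** Both are true. A gap of 2-5 points against a standard error of about 9 would seldom change a significance statement.
- **A reader might infer that a real CLAD benefit would be reversed or hidden.** The example does not show that, because the CLAD hazards are set equal and there is no benefit to reverse. Any gap in CLAD-free survival in such an example comes from the assumed deaths, which the Kaplan-Meier analysis of mortality already addresses.
- **A reader might infer that worst-rank scoring uncovers a QOL gain that the survivors-only test misses.** In a setting with 35% v 15% deaths and a true 0.3 SD gain, power is about 10% for survivors only and about 62% with deaths ranked worst. Much of the difference is mortality counted as QOL, as the roughly 26% rejection rate with no QOL effect shows. The contrast is not evidence of a QOL benefit.

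**Conclusion.** The concern holds in limited form. The document gives no account of death in the 48-month comparisons of CLAD and acute rejection or in the QOL comparisons at 24 and 48 months, while stressing poor survival and anticipating that the device lowers mortality. If deaths differ by arm, these comparisons tend to favour the arm with more deaths. Under the assumed rates, the effect is modest for CLAD and larger for QOL, where it also needs QOL and survival to be correlated.

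The direction relative to filtration is unknown before results: the device is penalised if it saves lives and flattered if it does not. The primary endpoint, sample size and interim analysis are unaffected. Making CLAD-free survival or worst-rank QOL the main analysis would be a choice of question with its own costs, not the correction of an error. This should be settled before outcomes by arm are known, but it does not threaten the main result.

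**What to change.** **CLAD and acute rejection.** Analyse time to CLAD and time to first acute rejection with cause-specific hazards and cumulative incidence, with death as a competing event. Show the cumulative incidence of death beside each. Report CLAD-free and rejection-free survival in support.

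**QOL.** Keep the Mann-Whitney test at 24 and 48 months, state that it is conditional on survival, and report it next to mortality by arm at the same time points. Add a sensitivity analysis with deaths ranked worst, labelled as a composite of survival and QOL.

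**Cost.** A few sentences in the analysis plan and a little extra analysis. CLAD, rejection and mortality are already collected by medical chart review, so no new data source is needed, provided that the event dates are entered. The sample size does not change. The price is more results to present, and the worst-rank analysis loses power when mortality is equal, which is why it belongs in the sensitivity set.

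### The only within-patient dependence named for repeated secondary outcomes is a patient random intercept; fitted as written in a linear model, it can misstate per-time and trend standard errors

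*Protocol article*

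**What the plan says.** The section Statistical Design, Method, and Analytical Procedures sets one approach for all repeated outcomes: "Continuous variables, ordered categorical variables, and binary variables measured over time will be compared using mixed models for repeated measures". If Q-Q plots show a problem, the distribution changes: "if the data are skewed, then a generalized linear mixed effects model with the appropriate distribution will be used". Two sentences then complete the specification: "A random intercept will be applied at the patient level" and "We will check model assumptions for each model". No residual covariance, random slope or robust standard error is named, and the target (per-time difference, trend or overall difference) is not stated. The section defers subgroups to the statistical analysis plan; it does not say that the within-patient structure is deferred.

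Under Secondary Performance End Points, the schedules are unequally spaced. Cytokines are taken "before and immediately after transplantation and at 6, 12, 24, 48, and 72 hours after transplantation", and lung volumes are "measured by spirometry at 1, 3, 6, 12, 24, and 48 months after transplantation". PGD severity is graded "using a rating scale from 0 to 3 on day 1, 2, and 3 after transplantation". The Sample Size section expects that "all secondary outcome variables will have a power of at least 80% at an α level of .05".

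**The concern.** A random intercept with independent, constant-variance residuals is compound symmetry. For spirometry it makes the correlation between months 1 and 3 equal to that between months 1 and 48. For cytokines it gives the samples around reperfusion the same variance as those at 72 hours. Two separate errors can follow:

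- **Per-time comparisons.** The model uses one pooled variance. If the true variance changes over time, standard errors are too small where it is high and too large where it is low. Decaying correlation alone does not cause this.
- **Trend and change comparisons.** The model uses one average correlation. If correlation decays with lag, or patients' slopes differ, standard errors for long-range contrasts are too small.

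The Q-Q check leads only to another distribution family. The general promise to check assumptions states no consequence if the covariance fits badly. Many of the 14 secondary end points are repeated measures, so both false claims and lost power are possible.

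**Working it through.** **The plan's own figures.** The article gives no figure for the repeated-measures analyses. Its sample size (52 evaluable and 58 recruited per group) concerns the primary end point and does not depend on this model.

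**Inputs.** From the article: six post-transplant cytokine times (0, 6, 12, 24, 48, 72 h), six spirometry times (1, 3, 6, 12, 24, 48 months), two-sided tests, and α = .05 for secondary outcomes. Assumed, because the article gives none: the SD at each time and the correlation between times. Data are taken as complete and samples as large.

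**Formulas.** Let v be the average variance over times and k the average covariance between different times. With balanced data and separate means for each arm and time, the random-intercept model assigns variance v to each time and v − k to each within-patient contrast c, multiplied by c'c. The true variance is c'Σc. If R is the model standard error divided by the true one, the false-positive rate at nominal 5% is 2 × [1 − Φ(1.96 R)].

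**Step 1: per-time comparison, six times, SD rising linearly.** R = √v / SD at that time.

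| Assumed SD range | √v | R, most variable | False positives | R, least variable | False positives |
|---|---|---|---|---|---|
| 0.8-1.0 | 0.903 | 0.903 | 7.7% | 1.128 | 2.7% |
| 0.7-1.0 | 0.856 | 0.856 | 9.3% | 1.223 | 1.7% |
| 0.6-1.2 | 0.923 | 0.769 | 13.2% | 1.538 | 0.3% |

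Counting the pre-transplant sample as a seventh time leaves these rates unchanged to within 0.1 percentage point. With constant SD, R = 1 at every time whatever the correlation pattern, so per-time tests keep 5%.

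**Step 2: spirometry, constant variance 1, correlation ρ^(gap in months / 12).**

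| ρ per 12 months | k | v − k | True slope variance ÷ c'c | R, slope | False positives, slope | R, month 48 − month 1 | False positives |
|---|---|---|---|---|---|---|---|
| 0.5 | 0.422 | 0.578 | 1.390 | 0.645 | 20.6% | 0.787 | 12.3% |
| 0.8 | 0.712 | 0.288 | 0.873 | 0.574 | 26.0% | 0.703 | 16.8% |

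For ρ = 0.5, the slope R is √(0.578 / 1.390) = 0.645. The true variance of the change is 2 × (1 − 0.5^(47/12)) = 1.868 against a model value of 2 × 0.578 = 1.156, so R = √(1.156 / 1.868) = 0.787.

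If correlation instead decays by visit number, AR(1) of 0.7-0.9 gives 17-21% for the slope in months. A joint 5-degree-of-freedom treatment-by-time test under ρ = 0.5-0.8 has about 8-9%, so the largest figures belong to the linear trend.

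**Step 3: where nothing goes wrong.** Under true compound symmetry every rate is 5%. The equally weighted average over times has R = 1 in every scenario, because its variance depends only on v and k.

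**Step 4: simulation check.** With 58 per arm, six visits and 4000 runs, AR(1) of 0.7 gave 17% for the slope and about 5% at the first and last visits. Compound symmetry of 0.5 with SD doubling gave 0.3% at the first visit and 13% at the last. Both agree with the formulas.

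**The case against.** A reader might infer that the article fixes the random intercept as the sole dependence term and that the secondary standard errors will therefore be wrong. The text does not support this. It never says the intercept stands alone, and a random intercept excludes neither a structured residual covariance nor a random slope. The label *mixed models for repeated measures* often goes with a specified covariance. The article condenses a longer protocol, and covariance structure is ordinary analysis-plan content. Assumption checks are promised for each model. No linear-trend or per-time contrast is named, so the largest rates above belong to tests that the plan may never run. No variances or correlations are given; ρ = 0.5 per 12 months implies a correlation of only about 0.07 between months 1 and 48. In a generalized linear mixed model with a non-identity link, a random intercept does not force equal variance on the outcome scale.

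All of this stands as a limit on the claim. It does not remove the point. The article does not merely leave the covariance open: it states one term, and an analyst who fits a linear model as written gets compound symmetry. The two readings can give materially different P values for the same data. The promised check names no consequence for covariance misfit.

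**Conclusion.** The point holds conditionally. If a linear mixed model is fitted with the stated random intercept and ordinary independent residuals, then:

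- per-time tests are wrong when variances differ over time: about 8-13% false positives at the most variable time and 0.3-2.7% at the least variable, under the assumed SD ranges;
- trend or change tests, if used, are anticonservative when correlation decays: about 21-26% for a linear trend and 12-17% for month 48 minus month 1, under the assumed 0.5-0.8 per 12 months.

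These are illustrations on assumed inputs, not estimates for this trial. The equally weighted time-average with complete data is unaffected. So are the primary end point (a regression on one value per patient), mortality (Kaplan-Meier) and quality of life (Mann-Whitney). Severity is low to moderate, for secondary outcomes only.

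**What to change.** For continuous repeated outcomes, replace the random-intercept sentence with a specification such as this: a mixed model for repeated measures with treatment, time, treatment-by-time and the stratification factors; post-baseline values as outcomes, with the pre-transplant value as a covariate where it is collected; unstructured within-patient covariance; Kenward-Roger degrees of freedom. Pre-specify a fallback for non-convergence that suits unequal spacing, for example a heterogeneous or spatial-power structure with robust standard errors. A visit-indexed AR(1) would treat the gaps from month 1 to 3 and from month 24 to 48 as equal.

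For binary and ordinal repeated outcomes, use robust standard errors. For every repeated outcome, name the target contrast: difference at a stated time, change, trend or average.

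The cost is a few sentences and no new data. Six times need 6 × 7 / 2 = 21 covariance parameters instead of 2, which should be workable with 116 patients. The main risk is non-convergence, which the fallback covers.
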